## Abstract

**Background:**

As the prevalence of hip pathology in the younger athletic population rises, the medical community continues to investigate effective intervention options. Femoracetabular impingement is the morphologically abnormal articulation of the femoral head against the acetabulum, and often implicated in pre-arthritic hip conditions of musculoskeletal nature. Arthroscopic surgical decompression and non-surgical rehabilitation programs focused on strengthening and stability are common interventions. However, they have never been directly compared in clinical trials.

The primary purpose of this study will be to assess the difference in outcomes between these 2 commonly utilized interventions for femoracetabular impingement.

**Methods:**

The study will be a single site, non-inferiority, randomized controlled trial comparing two different treatment approaches (surgical and nonsurgical) for FAI. The enrollment goal is for a total of 80 subjects with a diagnosis of Femoracetabular impingement that are surgical candidates and have failed 6 weeks of conservative treatment. This will be a convenience sample of consecutive patients that are Tricare beneficiaries and seeking care at Madigan Army Medical Center. Patients that meet the criteria will be screened, provide written consent before enrollment, and then randomized into one of two arms (Group I = hip arthroscopy, Group II = physical therapy). Group I will undergo hip arthroscopy with or without labral repair. Group II will follow an impairment based physical therapy program consisting of 2 sessions per week for 6 weeks. The primary outcome will be the Hip Outcome Score and secondary measures will include the International Hip Outcome Tool and the Global Rating of Change. Measures will be taken at baseline, 6 months, 1 and 2 years. Hip-related healthcare utilization between both groups will also be assessed at the end of 2 years.

**Discussion:**

The current evidence to support both surgical and conservative interventions for femoroacetabular impingement is based on low-level research. To date, none of these interventions have been directly compared in a randomized clinical trial. Clinical trials are needed to help establish the value of these interventions in the management of femoracetabular impingement and to help define appropriate clinical pathways.

**Trial registration:**

NCT01993615 30 October 2013.

**Electronic supplementary material:**

The online version of this article (doi:10.1186/s12891-016-0914-1) contains supplementary material, which is available to authorized users.

## Background

Femoracetabular impingent (FAI) consists of abnormal morphology of the acetabulum and/or proximal femur. This can result in cartilage injury as well as tears to the acetabular labrum [1–3]. The type of abnormal morphology is often separated into three categories, Cam (femoral neck), Pincer (acetabulum) and combined based on where the abnormality lies. This condition is encountered more commonly in younger active patients, and especially males. Some think it plays a role in the development of osteoarthritis, placing it within a pre-arthritic hip disease (PAHD) classification.

Because the diagnosis is strongly based on changes in bone morphology, radiographic imaging plays a significant role in the diagnosis, prognosis and surgical treatment of FAI. Common radiographic findings thought to aid in the diagnosis include measures of acetabular retroversion (crossover sign [1], ischial spine sign [2], and posterior wall sign [3]) and femoral neck angles and morphology (alpha angle [4], and pistol grip deformity [5]). These measures also assist with the planning for surgical interventions, and some authors have even linked radiographic findings with prognosis of FAI, such as the amount of radiographic joint space narrowing [6]. However, others studies point out the poor diagnostic accuracy of radiographic findings in the diagnosis of hip pathology, [7] and the potentially high prevalence of labral tears found in the asymptomatic population (as high as 73 %) [8, 9]. Others report very little diagnostic value in some of these same radiographic signs related to acetabular retroversion (crossover, ischial, and posterior wall) [10, 11].

This helps bring to light the diagnostic controversy related to FAI. If many of these radiographic anatomical variations help guide treatment decisions, but lack validity, then understanding optimal treatments for FAI becomes more challenging. The surgical approach focuses on addressing the anatomical impairments thought to cause the pathology. It has been referred to as a “hip preserving” intervention [12], that may potentially mitigate the onset of degenerative osteoarthritis. However, there is no evidence to suggest that progression of joint degeneration will not occur beyond what is expected in a morphologically normal control group [13, 14]. Only cohort-level studies have been performed to date, and these have reported favorable outcomes only in the short term [15–17]. Others caution about the significant variation in reported clinical and radiographic outcomes after surgery [15]. Zaltz and colleagues [18] warn that “indications and limits of arthroscopy must be carefully defined” and more research is needed to identify variables associated with failure rates and poor outcomes. Despite the challenges and controversy related to diagnosis, and lack of clinical trials to support surgical efficacy, surgery for the correction of FAI in the U.S. has increased significantly in the recent decade [9, 10]. This represents an eighteen-fold increase between 1999 and 2009 [11].

Conservative management is typically the precursor to most elective orthopaedic surgeries. Invasive surgical interventions are usually considered after conservative approaches have failed. However, there is also a large gap in the efficacy research of non-surgical interventions for FAI. Only low quality studies exist, consisting primarily of case studies and expert opinion [19–22]. Conservative management can include physical therapy, activity modification and avoidance of provocative hip positions [22]. There is no research beyond expert opinion to guide conservative physical therapy approaches to optimal management of FAI.

At present there are no randomized controlled trials that have compared surgery to a conservative intervention (e.g., physical therapy) for the treatment of FAI. Therefore, the primary purpose is to determine if there is a difference in self-reported functional outcomes between arthroscopic surgery and a supervised physical program for patients with FAI out at 2 years. The secondary aim is to evaluate the differences in hip-related healthcare utilization and associated costs between subjects in each group during the 2-year period following treatment.

## Methods/design

The study will be a single site, non-inferiority, randomized controlled trial comparing two different treatment approaches (surgical and nonsurgical) for FAI.

Potential subjects will be identified through the standard referral process to the orthopedic surgery and/or physical therapy clinic. Patients are referred through the computerized Composite Healthcare System (CHCS) by providers within the Madigan Army Healthcare System. An orthopedic surgeon at Madigan Army Medical Center (MAMC) will confirm that the patient is a candidate for hip arthroscopy prior to being considered for participation in the study (as outlined in the Inclusion/Exclusion Criteria). Research investigators and/or research assistants will ensure that potential subjects meet all inclusion and exclusion criteria prior to consent. All subjects will provide written informed consent before participating in the study. The protocol received ethics approval by the Madigan Army Medical Center Institutional Review Board. All interventions provided in this study are considered standard of care and could be given to a patient as part of their treatment plan even if they were not a part of this study. An ethics review will be conducted by Madigan Army Medical Center and monitored by the US Army Medical Department Clinical Investigation Regulatory Office to ensure compliance with federal regulations for protection of human medical research subjects. Participants can request to discontinue the study at any point.

Following consent, the investigators and/or research personnel will gather demographic information and objective measures for all subjects. A subject number will be assigned for each subject; all information collected will include the subject number only. All subjects will also complete a Hip Outcome Score (HOS), International Hip Outcome Tool Score, Global Rating of Change, Self Motivational Inventory, Pain Body Diagram, pain report via the Numeric Pain Rating Scale, and the Pain Catastrophizing Scale. The primary outcome measure will be the HOS at 2 years.

Subjects will then be randomized into one of two arms (Group I = Hip Arthroscopy, Group II = Physical Therapy). The method of group assignment will be determined via sequentially numbered opaque sealed envelopes. To minimize the risk of predicting the treatment assignment of the next eligible patient, randomization will be performed in permuted blocks of two or four with random variation of the blocking number. Date of enrollment will be used as the baseline date for both groups. Surgery will typically be scheduled within the following 3 months and physical therapy will typically be initiated within 1 to 2 weeks.

Group I will receive arthroscopy surgery. The hip arthroscopy will consist of acetabular rim trimming, labral repair or debridement and femoroplasty, all as indicated based on the surgeon’s clinical judgment with input from pre-operative imaging, exam findings and intra-operative findings. Typical surgery time is approximately 2 h in duration; surgery time may fluctuate up to 60 min depending on the complexity of the surgery. Hip arthroscopy is typically a same-day surgery; however subjects may require an overnight stay at the discretion of the orthopedic surgeon. This is standard for how a patient would receive this intervention outside of the study.

Following surgery, subjects will be evaluated by a physical therapist in the MAMC outpatient physical therapy clinic within 7 days to begin post-operative rehabilitation (Additional file 1). Typical post-operative rehabilitation is completed within 6 months following surgery; however additional care may be required at the discretion of the physical therapist. Subjects within this group will follow up with a research investigator and/or research assistant at MAMC to complete outcome measures following surgery at 6 month, 1 year and 2 year time periods.

Group II will receive a standardized physical therapy program that is supervised in the clinic for 6 weeks. Subjects will participate in two 45-min physical therapy visits a week for 6 weeks, for a total of 12 sessions. The physical therapy treatment plan will be based on individual impairments identified during the initial evaluation (Additional file 2). Typical treatment for FAI includes hip mobilizations (Additional file 3) and therapeutic exercise (Additional files 4 and 5), however other treatment interventions may be implemented at the discretion of the physical therapist.

After 12 sessions of physical therapy, patients will be released from treatment. Subjects can follow-up with their primary care provider for any additional specialty care referrals, to include orthopedics and physical therapy. Subjects will be analyzed in the groups they were originally randomized to.

Subjects will follow-up with a research investigator or research assistant that is unaware of the treament allocation, in order to complete outcomes measures at 6 month, 1 and 2 year time periods following the initial physical therapy evaluation.

This will be a single center randomized controlled trial with sequential enrollment of a convenience sample, with concealed allocation and blinded outcome assessors. The independent variable is treatment (physical therapy or arthroscopic surgery) and time with 4 levels out to 2 years. We will analyze any potential covariates that may affect prognosis, to include internal motivation and psychosocial beliefs using the Self Motivation Inventory scale and the Pain Catastrophizing Scale. This will be a trial assessing pragmatic delivery of two common interventions, and will report results following CONSORT guidelines for pragmatic trials [23]. The current SPIRIT guidelines for creating protocols for randomized clinical trials were followed in deriving the protocol [24]. Figure 1 demonstrates the flow of subjects through the trial.

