### Justification of sample size

Our power analysis was based on the effect size reported by Martin and colleagues [33] for the Hip Outcome Score. They reported MCID values of 9 and 6 points for the Activities of Daily Living (ADL) and sports subscales respectively [33]. In order to detect a significant change between groups that is clinically meaningful, we will need to enroll 20 subjects per group based on the effect size of the ADL subgroup in the Martin study. This derived minimum sample size will provide us statistical power of 80 % with an alpha of 0.05. This is the more conservative analysis. However, the follow-up time period in the referenced study was only out to 6 months whereas this study will be out to 2 years. Accounting for 10 % loss to follow-up per year, which often happens in active duty military populations that deploy or get reassigned to multiple posts, we will plan on recruiting 80 subjects.

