### Data analysis

The primary analysis of effectiveness will be performed using a linear mixed-effects model that is flexible in accommodating data that is assumed to be missing at random. There will be 4 time points for measurement of each outcome (baseline, 6, 12, and 24 months). Subjects will be analyzed in the groups that they were originally allocated to. Sensitivity analyses will be performed to assess the impact of treatment cross over in the results. Descriptive statistics will be computed to characterize and compare the 2 treatment groups for assessment of baseline heterogeneity. Distributions of measured variables will be examined visually with frequency histograms and formally assessed with Kolmogorov-Smirnov and Shapiro-Wilk statistics to test the normality assumption. Levene’s test will be used to assess for violations of the homogeneity of variance assumption. Baseline comparability of groups will be tested with chi-square statistics for categorical variables and with unpaired t-tests if parametric assumptions are satisfied; Mann–Whitney U tests otherwise. All statistical tests will be performed at an alpha level of 0.05.

If one treatment is shown to be superior to the other, supplemental analyses will be performed by dichotomizing groups based on minimal clinically important differences (MCIDs) of 9 for HOS and +3 points for GROC scores. This will allow computation of absolute risk reduction, relative risk reduction, and number needed to treat (with associated 95 % confidence intervals) using failure to obtain clinically meaningful benefit as the event of interest.

Healthcare Utilization will be extracted from the Department of Defense Military Health System Data Repository (MDR) database which is the most commonly used system operated by TRICARE for research, containing direct and purchase care data. The amount and type of healthcare associated with an FAI-related diagnosis, along with related cost, will be abstracted for every patient in the study. This will include diagnostic imaging tests, medications, and specialty referrals. The amount of utilization for each category will be compared between groups.

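### The protocol declares a non-inferiority trial, but its purpose and sample size are those of a test of difference, and no margin or reference arm is given

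*Protocol article*

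**What the plan says.** The Abstract (Methods) and the first sentence of Methods/design give the same design label: "The study will be a single site, non-inferiority, randomized controlled trial comparing two different treatment approaches (surgical and nonsurgical) for FAI".

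Three other sections describe a different question.

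- Background: "the primary purpose is to determine if there is a difference in self-reported functional outcomes between arthroscopic surgery and a supervised physical program".
- Justification of sample size: "In order to detect a significant change between groups that is clinically meaningful, we will need to enroll 20 subjects per group". The effect comes from a cited study: "They reported MCID values of 9 and 6 points for the Activities of Daily Living (ADL) and sports subscales respectively". The ADL value is the one used, with 80% power and alpha 0.05.
- Data analysis: a linear mixed-effects model by randomised group, all tests at alpha 0.05, and then "If one treatment is shown to be superior to the other, supplemental analyses will be performed".

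On the endpoint, Methods/design says: "The primary outcome measure will be the HOS at 2 years". Nowhere does the article name the arm that serves as reference, or the loss on the HOS that would be tolerable.

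**The concern.** A non-inferiority trial and a test of difference have different null hypotheses. The first rejects a deficit at least as large as a stated margin. The second rejects equality. The label promises the first, while the purpose and the power statement describe the second.

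This goes beyond detail that a condensed article leaves to its full protocol or SAP. The article states its objective and the basis of its sample size, and both conflict with the design it declares. A SAP consistent with one side would contradict the other.

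What is at stake is how the main result is read. Under a non-inferiority label, a p-value above 0.05 invites the conclusion that physical therapy is no worse than surgery. A test of difference gives no error control for that conclusion.

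**Working it through.** **1. The passages side by side**

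| Element | What the article states | Fits non-inferiority? |
|---|---|---|
| Design label (Abstract; Methods/design) | Non-inferiority | Yes |
| Primary purpose (Background) | Whether a difference exists | No |
| Sample-size aim | Detect a significant between-group difference | No |
| Role of the 9 points (sample size) | Effect to detect | Not used as a margin |
| Alpha (Data analysis) | 0.05, sidedness not stated | Neutral |
| Superiority sentence (Data analysis) | Conditional trigger for extra analyses | Weak evidence either way |
| Margin, reference arm | None | No |

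The contradiction rests mainly on the purpose and the sample-size aim.

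**2. The plan's own figure**

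The stated 20 per group cannot be reproduced, because no SD is given. It can only be solved for the SD. For a two-sample t-test with 20 per arm, two-sided alpha 0.05 and 80% power, the standardised difference is 0.909. With 9 points as the difference, SD = 9 / 0.909 = 9.9. The normal approximation gives 0.886 and SD = 9 / 0.886 = 10.2.

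**3. Evaluable patients**

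40 per arm (Table 1), with 10% lost per year over 2 years: 40 × 0.80 = 32, or 40 × 0.9 × 0.9 = 32.4. I use 32.

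**4. False-claim rate if p > 0.05 were read as non-inferiority**

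Assume a true deficit of 9 points. SE = SD × √(2/n). The rate is the probability that a two-sided t-test at 0.05 is non-significant, from the non-central t distribution with 2n − 2 degrees of freedom and non-centrality 9/SE.

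| n per arm | SD | SE | 9/SE | P(p > 0.05) |
|---|---|---|---|---|
| 32 | 9.9 (implied) | 2.475 | 3.64 | 5% |
| 32 | 15 (assumed) | 3.75 | 2.40 | 34% |
| 32 | 20 (assumed) | 5.00 | 1.80 | 57% |
| 40 | 9.9 (implied) | 2.214 | 4.07 | 2% |

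The comparator is the 2.5% of a one-sided non-inferiority test based on a 95% confidence limit. The normal approximation, Φ(1.96 − 9/SE) − Φ(−1.96 − 9/SE), gives 5.7%, 33% and 56% at 32 per arm with SDs of 10.16, 15 and 20, and 2.3% at 40 per arm with SD 10.16.

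**5. Is the sample size itself wrong for non-inferiority?**

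Not necessarily. With margin M, true difference zero, one-sided 0.025 and 80% power, n per arm = 2 × SD² × (1.96 + 0.84)² / M². This is the two-sided superiority formula with M in place of the difference. At M = 9 and SD 10 it gives 2 × 100 × 7.84 / 81 = 19.4, so 20 per arm. At SD 15 it gives 44 and at SD 20 it gives 78.

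**The case against.** The strongest reply is that a non-inferiority trial may go on to test superiority, that alpha 0.05 is compatible with either design, and that a confidence-limit rule is detail an article may leave out. Each of these stands, so neither the alpha level nor the superiority sentence proves much. The stated purpose and the sample-size aim remain, and neither can be read as a non-inferiority hypothesis.

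The size of the error rate also depends on inputs the document does not give. At the only SD that can be tied to the plan's figures, the rate is about 5% or 2%, not far from 2.5%. The 34% and 57% rest on assumed SDs. The calculation uses a two-sample t-test, and the planned mixed model over four time points may be more precise. That stands. The rate is uncontrolled, but not always inflated.

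Three stronger readings are tempting, and the document supports none of them.

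- A reader might infer that the trial will report non-significance as non-inferiority. No section says so; it is a risk.
- A reader might infer that the numbers could never support non-inferiority. Step 5 shows that with a 9-point margin the two designs need the same n. The gap is the missing margin and decision rule.
- A reader might infer that, with a large SD, no non-significant result could exclude a 9-point deficit. Non-inferiority looks at one limit only. At SD 20 and 32 per arm (half-width 10 points), an estimate 3 points in favour of physical therapy gives an interval from 7 points worse to 13 points better. That is non-significant, yet it excludes a 9-point deficit. With no true difference, about 40% of such trials would give a non-significant result that does so.

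**Conclusion.** The design label is wrong as written. The article declares non-inferiority, while its purpose and sample-size basis are those of a test of difference and it gives no margin or reference arm. The design as stated does not support a non-inferiority conclusion. The comparison by randomised group remains valid as a test of difference.

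If non-significance were read as non-inferiority, the false-claim rate at a true 9-point deficit would range from about 2% (SD 9.9, 40 per arm) through 5% (SD 9.9, 32 per arm) to 34% and 57% (SDs 15 and 20, 32 per arm). The range assumes a two-sided t-test and a 9-point deficit. The SD of 9.9 is back-calculated, and 15 and 20 are illustrations. The internal contradiction depends on none of these figures. Because it concerns how the primary result will be interpreted, it should be corrected even though the remedy is small.

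**What to change.** In the Abstract and in Methods/design, replace the word non-inferiority with superiority (two-sided), so that the label matches Background, Justification of sample size and Data analysis. Add to Data analysis that the conclusion is drawn from the two-sided 95% confidence interval for the 24-month HOS difference, and that a non-significant difference will not be interpreted as non-inferiority or equivalence. This is a change of wording only. It needs no further patients or data, and the trial gives up a label its stated design does not support.

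If non-inferiority is truly intended, change the other side instead. Rewrite Background, Justification of sample size and Data analysis with a named reference arm, a justified margin on the HOS, a confidence-limit rule, and a sample size with its SD that matches them. This option may not be free. Even with a margin as wide as 9 points, step 5 gives 20 evaluable per arm at SD 10, but 44 at SD 15 and 78 at SD 20, against about 32 expected.

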### Outcome measures

The primary outcome will be the Hip Outcome Score. Secondary outcome measures will include the iHOT33, GROC, and NPRS. These will all be taken at baseline, 6, 12, and 24 months. The Self Motivation Inventory and Pain Catastrophizing Scale will also be taken at baseline and at 24 months. For our healthcare utilization analysis, we will collect healthcare utilization and associated costs that occurred for the duration of the study, and compare them between groups. We will be using the Military Health System Data Repository (MDR) for abstraction of data.

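### Follow-up is timed from enrolment, from surgery and from the first physical therapy evaluation, so the date of the 2-year primary outcome is not fixed

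*Protocol article*

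**What the plan says.** Methods/design contains three time origins.

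- **Enrolment, both arms:** "Date of enrollment will be used as the baseline date for both groups".
- **Surgery, Group I:** these patients return "to complete outcome measures following surgery at 6 month, 1 year and 2 year time periods".
- **First therapy evaluation:** directly after the description of the Group II programme, subjects are to "complete outcomes measures at 6 month, 1 and 2 year time periods following the initial physical therapy evaluation". The sentence does not name Group II; its position makes that the natural reading.

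The same section gives the delay from enrolment to treatment: "Surgery will typically be scheduled within the following 3 months and physical therapy will typically be initiated within 1 to 2 weeks".

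The primary endpoint carries no origin: "The primary outcome measure will be the HOS at 2 years". Table 1, Outcome measures and Data analysis list 6, 12 and 24 months, also without an origin. Methods/design and Data analysis both keep patients in their allocated group.

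The healthcare utilisation window is also described in two ways. The secondary aim in Background compares use and costs "between subjects in each group during the 2-year period following treatment", while Outcome measures says "we will collect healthcare utilization and associated costs that occurred for the duration of the study".

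**The concern.** The two visit sentences are the specific instructions for follow-up, and each starts the clock at an event that happens after randomisation and at a different delay in each arm. Staff who follow them would assess the arms at different times from randomisation. The analysis treats time as four nominal levels, so it would pool those visits as the same time point.

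Surgery is also an event that some Group I patients may never reach. The Discussion itself describes crossover as a common concern in trials of this kind. Under the surgery clock such a patient has no date from which to count 24 months, yet the as-randomised analysis needs that patient's score.

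This is a conflict between statements in the article, not detail left to a fuller document. Visits already held on mixed clocks cannot be re-dated afterwards.

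**Working it through.** The plan gives no figure for this point that could be reproduced, so the check is to apply each rule to the stated delays.

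**Inputs (Methods/design)**
- Nominal visits: 6, 12 and 24 months.
- Enrolment to surgery: 0 to 3 months, reading the typical limit as the upper end.
- Enrolment to first therapy session: 1 to 2 weeks. With 1 week = 7/30.4375 = 0.23 month, that is 0.23 to 0.46 month.
- Assumptions: the first therapy session and the initial therapy evaluation coincide, and enrolment and randomisation fall on about the same day.

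**Treatment-based clocks**

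Months from enrolment = nominal visit + delay to the anchor.

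| Visit | Surgery | Physical therapy | Gap if surgery is at 3 months |
|---|---|---|---|
| 6 | 6.0 to 9.0 | 6.23 to 6.46 | 2.54 to 2.77 |
| 12 | 12.0 to 15.0 | 12.23 to 12.46 | 2.54 to 2.77 |
| 24 | 24.0 to 27.0 | 24.23 to 24.46 | 2.54 to 2.77 |

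For example, at 24 months: 27 − 24.46 = 2.54 and 27 − 24.23 = 2.77. If surgery took place at once, the surgery visit would come slightly earlier than the therapy visit (24 − 24.46 = −0.46 month). About 2.8 months is therefore the upper end of the range, not a typical value.

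The absolute gap is the same at every visit, so its relative size falls with time: 2.77/6.23 = 44% at 6 months, 2.77/12.23 = 23% at 12 months and 2.77/24.23 = 11% at 24 months.

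**Enrolment clock**

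Both arms are assessed at 6, 12 and 24 months from enrolment, so the gap is 0. Time since treatment start then differs instead:

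- At 6 months: 6 − 3 = 3 to 6 months for surgery; 6 − 0.46 = 5.5 to 6 − 0.23 = 5.8 months for therapy.
- At 24 months: 21 to 24 months for surgery; 23.5 to 23.8 months for therapy.

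**Worst-case illustrations, conditional on the treatment-based clocks**

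- Extra loss to follow-up at the 10% per year in Justification of sample size: 10% × 2.54/12 = 2.1 to 10% × 2.77/12 = 2.3 percentage points. That is about 0.8 to 0.9 of a patient in 40, if every operation takes place at 3 months.
- Patients without a visit date: the Discussion cites 6% of surgery-assigned patients not operated on by 6 months in a knee trial, and roughly 40% crossover in each group of a spine trial. Applied to 40 patients: 0.06 × 40 = 2.4 and 0.40 × 40 = 16. These are other conditions, so the range shows sensitivity and is not a forecast for this trial.

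**The case against.** The strongest reply is that the enrolment sentence is the only one that expressly covers both groups, and on that reading there is no gap. The Group I wording could describe sequence (measures are taken after surgery) rather than a time origin, and the therapy sentence says only subjects. This makes the imbalance conditional. It does not remove the conflict: the enrolment sentence mentions no visits, while the other two do. If the therapy sentence were meant for both arms, it would contradict the surgery sentence outright.

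A reader might go further and infer that surgery-arm patients who are never operated on have no 2-year visit. The protocol does not say so. Table 1, Outcome measures and Data analysis schedule 24-month measurement without exempting them, and each has an enrolment date. Only under the surgery clock is their visit date undefined.

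A reader might also infer that the as-randomised comparison is broken. Analysis by allocated group is stated and does not depend on visit timing. What may differ is when the outcome is measured.

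Finally, the Background wording on utilisation could be read as leaving out pre-operative care and the operation itself. The operational text points the other way: Outcome measures covers the whole study, and Data analysis abstracts care and cost linked to an FAI diagnosis for every patient. The two descriptions of the window still need aligning, but this is a minor, secondary matter.

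**Conclusion.** The inconsistency is real and bears on when the primary endpoint is measured. Its consequence depends on which rule staff follow: no gap if enrolment governs; otherwise up to about 2.8 months at each visit, on the stated typical delays and with surgery at the 3-month limit. Operations later than that would widen it. Under the surgery clock, unoperated Group I patients also lack a defined visit date.

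The likely effect on the 24-month Hip Outcome Score is modest, because a shift of at most about 11% in follow-up time comes late in follow-up. The 6-month comparison is more exposed. The documents do not support stating as fact that the arms are measured at different times. This should be fixed, but it does not by itself undermine the primary comparison.

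**What to change.** State one origin, the date of enrolment/randomisation, for all 6-, 12- and 24-month visits in both arms, and say which of the two dates is meant if they can differ. This agrees with the baseline rule already in Methods/design and with the as-randomised analysis, and it gives every randomised patient a dated 2-year visit, operated on or not.

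- In Methods/design, remove surgery and the first therapy evaluation as visit anchors.
- In Background and Outcome measures, define the utilisation window identically: 24 months from randomisation, including the index procedure.
- Record the dates of surgery and of the first therapy session, and report time since treatment descriptively.

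This is a wording amendment; it changes no treatment and adds no patients. The one downside is that surgery patients would be about 3 to 6 months past their operation at the 6-month visit. Since Methods/design expects post-operative rehabilitation to take up to 6 months, some would still be in rehabilitation then. That is a true feature of the surgical strategy as delivered and can be shown through the recorded treatment dates.
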